## Abstract

**Background::**

Female pelvic floor dysfunction is one of the common chronic diseases affecting women's physical and mental health. Pregnancy and delivery are one of the main causes. Pelvic floor rehabilitation is a common method for the treatment of postpartum pelvic floor dysfunction, but it has some defects. Acupoint injection has advantages in the treatment of postpartum pelvic floor dysfunction, but there is a lack of standard clinical research to verify it. Therefore, the purpose of this randomized controlled trial is to evaluate the efficacy and safety of acupoint injection combined with pelvic floor rehabilitation in the treatment of postpartum pelvic floor disorders.

**Methods::**

This is a prospective randomized controlled trial to study the efficacy and safety of acupoints injection combined with pelvic floor rehabilitation. And it is approved by the Ethics Committee of Clinical Research of our hospital. Patients were randomly divided into observation group (acupoint injection combined with pelvic floor rehabilitation group) or control group (pelvic floor rehabilitation group alone). The patients were followed up for 8 weeks after 12 weeks of treatment. The observation indexes included: pelvic organ prolapse degree, pelvic floor muscle strength, urinary incontinence score, adverse reactions, among others. Data were analyzed using the statistical software package SPSS version 18.0.

**Conclusions::**

This study will evaluate the efficacy and safety of acupoint injection combined with pelvic floor rehabilitation in the treatment of postpartum pelvic floor dysfunction, and provide reliable reference for the clinical application of this project.

**Trial registration::**

OSF Registration number: DOI 10.17605/OSF.IO/VC65Z

## Introdoction

1

Pelvic floor dysfunction (PFD) refers to a group of diseases caused by weak supporting tissue of the pelvic floor, including pelvic organ prolapse (POP), stress urinary incontinence, sexual dysfunction, and so on.^[1]^ In China, the incidence of PFD in women is as high as 58.7%, of which POP is the most common (48.73%), followed by stress urinary incontinence (8.7%).^[2]^ Although PFD is not like a malignant tumor endangering the lives of women, because of the special nature of PFD, patients often suffer from great psychological pressure,^[3]^ It has become 1 of the 5 most common chronic diseases affecting women's physical and mental health and quality of life.^[4]^

The pathogenesis of PFD is complex. Previous clinical studies have shown that pelvic floor muscle injury and pelvic floor connective tissue relaxation caused by various causes are its main pathogenesis.^[5]^ Pregnancy and delivery can lead to impaired pelvic floor muscle function, reduced pelvic floor muscle strength, and further cause urinary incontinence, pelvic organ prolapse, and other pelvic floor dysfunction diseases.^[6]^

Acupoint injection is a kind of alternative therapy based on Chinese meridian theory, which injects drugs into specific acupoints and achieves the purpose of treatment by stimulating acupoints.^[7]^ It is found that acupoint injection can improve the function of pelvic floor circulation, improve muscle strength and muscle tension, and accelerate nerve conduction.^[8]^ Pelvic floor rehabilitation training is a first-line conservative treatment for the prevention and treatment of pelvic floor disorders.^[9]^ By exercising the muscles, the patient can increase the muscle volume and raise the levator plate and genital hiatus, thus improving the support of pelvic organs.^[10]^ At present, there is a lack of clinical research on acupoint injection combined with pelvic floor rehabilitation in the treatment of postpartum pelvic floor disorders. Therefore, we designed this randomized controlled trial to evaluate the efficacy and safety of acupoint injection combined with pelvic floor rehabilitation in the treatment of postpartum female pelvic floor disorders.

## Materials and methods

2

### Study design

2.1

This is a prospective, single-center, randomized controlled trial to study the efficacy of pelvic floor rehabilitation combined with acupoint injection in the treatment of postpartum pelvic floor disorders. It was approved by the Ethics Committee of Traditional Chinese Medicine. This trial will follow the comprehensive trial reporting standard,^[11]^ and comply with Standard Protocol Recommendations for Interventional Trials 2013 Statement.^[12]^ The flow chart of the study is shown in Figure 1.

**Figure 1 F1:**
[figure not shown]
Flow diagram.

This research scheme is in line with the Helsinki Declaration and approved by the Clinical Research Ethics Committee of our hospital. This laboratory is registered in the open science framework (OSF) (registration number: DOI 10.17605/OSF.IO/VC65Z). Before being randomly divided into groups, all patients need to sign a written informed consent form, and they are free to choose whether or not to continue the trial at any time.

### Patients

2.2

Inclusion criteria were: age 22 to 45 years’ old; Primipara who is full-term and vaginal delivery; the examination was in accordance with the diagnostic criteria of PFD within 180 days after delivery; pelvic floor muscle ≤III level, POP international quantitative framework dividing ≤II degrees; participate voluntarily and sign the informed consent form.

Exclusion criteria were: patients with previous history of reproductive system surgery; patients with neurological diseases, respiratory dysfunction, and vital organ dysfunction; patients with PFD disease before pregnancy; patients with a history of severe uterine malformation; patients with allergy or contraindications to the medication used in this study.

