### Sample size

2.3

The calculation of sample size is based on mean and standard deviation of muscle strength scores of class I muscle fibers in pelvic floor muscles after treatment. According to the results of the pilot study, the experimental group was 19.37 ± 2.26, and the control group was 21.01 ± 2.57. Set α = 0.025, unilateral test, β = 0.20. According to the calculation of PASS15.0 software, 36 participants are needed in each group; the estimated withdrawal rate is 10%, so that 40 participants will be included in each group.

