### Randomization and blinding

2.4

In this study, patients meeting the research criteria were included through pre-hospital recruitment and inpatient screening. The random number generator in Microsoft Excel was used to randomly divide the patients into the observation group and the control group according to the proportion of 1:1. The clinical research coordinator entered participant information on the tablet and was given a random number. The research assistant got the allocation of participants from the computer. Throughout the study, the research assistant was responsible for screening, recruiting participants, and assigning random numbers to participants who had been included. Outcome evaluator was responsible for the evaluation of the scale. Given the practical nature of acupoint injection, participants and practitioners might be aware of random assignment. However, the evaluators of the research results, the statisticians of data statistics and analysis did not know about the distribution.

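### The 180-day window is tied to the diagnostic examination rather than to randomisation, and time since delivery is then left as noise in an unadjusted comparison

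*Protocol article*

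**What the plan says.** **Eligibility (Protocol article, 2.2 Patients).** The only time criterion is that "the examination was in accordance with the diagnostic criteria of PFD within 180 days after delivery". No minimum time since delivery is given. No section limits the interval from delivery, or from that examination, to randomisation or start of treatment.

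**Recruitment and allocation (2.4 Randomization and blinding).** The article says that "patients meeting the research criteria were included through pre-hospital recruitment and inpatient screening". Allocation is 1:1 and is described in these words: "The random number generator in Microsoft Excel was used to randomly divide the patients". No strata or blocks are mentioned.

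**Endpoint behind the sample size (2.3 Sample size).** The calculation uses the "mean and standard deviation of muscle strength scores of class I muscle fibers in pelvic floor muscles after treatment", with pilot values "the experimental group was 19.37 ± 2.26, and the control group was 21.01 ± 2.57" and "Set α = 0.025, unilateral test, β = 0.20". It arrives at 36 per group, or 40 after 10% withdrawal.

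**Timing and analysis (2.5.1, 2.7, 2.8).** Treatment lasts 12 weeks. Baseline data are collected before treatment starts, without reference to days since delivery. Continuous outcomes are compared by the Mann-Whitney test, which takes no covariate.

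**The concern.** The Introduction attributes reduced pelvic floor muscle strength to pregnancy and delivery. The Discussion says vaginal delivery stretches and damages type I and type II fibres. The sample size rests on class I fibre strength after treatment. By the article's own reasoning, then, distance from delivery is a plausible prognostic factor for the variable that sizes the trial.

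The criterion as worded leaves that distance loosely controlled. It could be short, because there is no lower limit. It could exceed 180 days at randomisation, because only the examination is bounded. Two recruiters could apply the sentence differently, and the choice of who was enrolled cannot be repaired afterwards.

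Two things are at stake: a clear definition of the population, and precision in a trial of 80 women whose stated analysis ignores a variable that follows from the delivery date.

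**Working it through.** **1. The plan's own sample size.** Inputs from 2.3: absolute difference 21.01 − 19.37 = 1.64; SDs 2.26 and 2.57; one-sided α 0.025; power 80%.

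- Pooled SD = √[(2.26² + 2.57²)/2] = √5.86 = 2.42; standardised difference = 1.64/2.42 = 0.678.
- The normal approximation gives 35 per group. The t-test version gives 35.2, so 36. Then 36/0.90 = 40.

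The stated figures reproduce, and this point does not touch them.

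**2. Width of the window.** 12 weeks = 84 days; 180/84 = 2.1. The span in which the examination may fall is about twice the treatment period.

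**3. Sampling error already in the design.** With 36 per arm, the 95% range of the difference in means is 1.96 × 2.42 × √(2/36) = ±1.12. Any chance imbalance in time since delivery is part of this range if the pilot SDs reflect a similar mix of women.

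**4. How large a chance imbalance could be.** Assumption, not in the document: time since delivery uniform over 0 to 180 days.

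- SD = 180/√12 = 52 days.
- 95% range of the difference between arm means = 1.96 × 52 × √(2/36) = ±24 days.
- The chance of a difference of 14 days or more is 25%.

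**5. What it could mean for the outcome.** Let ρ be the correlation of time since delivery with post-treatment strength within arm. The document gives no value, so a range is shown. Share of variance = ρ². The 95% chance shift is ρ × 1.12, set against 1.64. The range left after adjustment is 1.12 × √(1 − ρ²).

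| assumed ρ | share of outcome variance | 95% chance shift | as % of 1.64 | ±1.12 becomes |
|---|---|---|---|---|
| 0.1 | 1% | ±0.11 | 7% | ±1.11 |
| 0.3 | 9% | ±0.34 | 20% | ±1.07 |
| 0.5 | 25% | ±0.56 | 34% | ±0.97 |

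The shifts lie inside the ±1.12 and are not added to it. The last column is what adjustment for days since delivery alone could recover. If baseline strength is also in the model, it may already carry part of that gain.

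**6. Type I error.** With no treatment effect, both arms are draws from the same mixed population, so the test keeps its level whatever ρ is. Simulation agrees: 4,000 runs each at ρ = 0, 0.3 and 0.5, with 36 per arm, gave Mann-Whitney rejection in 4.5%, 5.1% and 5.8% against a nominal 5%. The simulation standard error is √(0.05 × 0.95/4000) = 0.3 percentage points.

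**The case against.** The strongest reply is that chance imbalance is not a defect. Randomisation makes the comparison fair on average, the test allows for the variation, and the same could be said of any prognostic factor in any unstratified trial of 80. This stands, and it limits the point to precision and clarity of definition.

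Several stronger readings are tempting, and the document does not support them:

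- **That imbalance alone could move the result by nearly half the planned effect.** Suppose half the women are early postpartum and early and late women differ by 3.28, twice the planned difference. A 95% imbalance of 1.96 × √(2 × 0.25/36) = 0.23 then gives a shift of 0.76, or 46% of 1.64. But such a split contributes 0.25 × 3.28² = 2.69 to a total variance of 5.86. Early or late status alone would have to explain 46% of all outcome variance.
- **That faster recovery in early women translates directly into the endpoint.** The trial is sized on strength after treatment, not on change. If early women start weaker, faster recovery may only close the gap.
- **That natural recovery dilutes the contrast.** Recovery common to both arms cancels in the difference. Dilution would need a ceiling effect or an interaction.
- **That women are enrolled on the maternity ward days after birth, or long after diagnosis.** Inpatient screening is not said to mean a maternity ward, and the article gives no sign of long delays. Nor does it say how quickly weakness resolves.

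It is also fair that stratification or adjustment may be set out in a document not shown. The eligibility sentence is in the article, however, and so is the unadjusted test. A loose reading, enrolment within 180 days, is possible, but it would still set no lower limit.

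**Conclusion.** The point holds as one of definition and efficiency. As worded, the window does not fix time since delivery at randomisation, and the described allocation and analysis neither balance nor use it. Validity is not threatened.

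The size cannot be estimated from the document, which reports neither the natural course of recovery nor the postpartum range of the pilot. At an assumed correlation of 0.1 the loss is negligible; at 0.5 it is worth having back. The chance-shift and precision figures rest on those assumed correlations, on 36 analysed per arm and on the pilot SDs; the ±24 days also rests on the uniform spread. Severity is minor to moderate: a cheap improvement rather than a flaw that would invalidate the trial.

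**What to change.** 1. **Reword the criterion in 2.2** as days from delivery to randomisation, stating a lower and an upper limit. The article offers no basis for particular values, so the sponsor should set and justify them.
2. **Confirm muscle grade and prolapse degree at the pre-treatment assessment** already planned in 2.7. Section 2.6.2 lists amplitude and fatigue rather than grade, so the grade may need to be recorded there as well.
3. **Replace the unadjusted Mann-Whitney test for post-treatment strength** with a linear model containing treatment, baseline strength and days since delivery. This compares means, as the sample-size calculation does, and needs no change to the 36 or the 40.
4. **Optionally, stratify the list by time since delivery**, with blocks within strata; strata without blocks would not balance the arms.

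Cost: one reworded sentence, one covariate computed from the delivery date, and a changed test with the usual assumptions of a linear model. A few women may need re-checking or a later start.

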### Sample size

2.3

The calculation of sample size is based on mean and standard deviation of muscle strength scores of class I muscle fibers in pelvic floor muscles after treatment. According to the results of the pilot study, the experimental group was 19.37 ± 2.26, and the control group was 21.01 ± 2.57. Set α = 0.025, unilateral test, β = 0.20. According to the calculation of PASS15.0 software, 36 participants are needed in each group; the estimated withdrawal rate is 10%, so that 40 participants will be included in each group.

### Randomization and blinding

2.4

In this study, patients meeting the research criteria were included through pre-hospital recruitment and inpatient screening. The random number generator in Microsoft Excel was used to randomly divide the patients into the observation group and the control group according to the proportion of 1:1. The clinical research coordinator entered participant information on the tablet and was given a random number. The research assistant got the allocation of participants from the computer. Throughout the study, the research assistant was responsible for screening, recruiting participants, and assigning random numbers to participants who had been included. Outcome evaluator was responsible for the evaluation of the scale. Given the practical nature of acupoint injection, participants and practitioners might be aware of random assignment. However, the evaluators of the research results, the statisticians of data statistics and analysis did not know about the distribution.

### Study design

2.5

#### Pelvic floor rehabilitation

2.5.1

Pelvic floor rehabilitation consisted of 10 maximal voluntary contractions maintained for at least 6 seconds. At the end of a set of 10 contractions, 5 rapid contractions were performed. The interval between contractions was 6 seconds. This training can be done in lying, seated, kneeling on all fours, and standing positions. Two professional physiotherapists will provide face-to-face coaching training to the participants twice a week for 12 weeks.

In addition to completing face-to-face training with the therapist twice a week, all participants will be asked to follow the written instructions at home every day and record the frequency. A monitoring meeting will be held once a week, and professional physiotherapists will conduct new assessments and guidance according to the intensity, frequency, and timing of the participants’ training.

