#### Acupoint injection

2.5.2

The patient took a suitable position, exposed the skin of abdomen, waist and leg and located Guanyuan, Zusanli, and Sanyinjiao. After local disinfection, a 10 mL syringe was used to connect the No. 7 needle, and the needle was punctured slowly at the vertical acupoints. After the patient felt the sensation of acid swelling and no blood return after aspiration. Inject the medicine and about 0.5 to 1 mL was injected into each point. The acupuncture depth was about 2 to 3 cm. Drug composition: Huang Qi injection (China Wuxi SFDA approval number: Z32021030). After the injection, lie prone and rest for 30 minutes to observe whether the patient felt uncomfortable. The injection procedure was performed by the same doctor with >5 years of acupoint injection experience.

The observation group was combined with acupoint injection on the basis of pelvic floor rehabilitation training, whereas the control group was simply given rehabilitation training.

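### The physiotherapists who guide the shared rehabilitation each week are not among those kept unaware of allocation, although the reason given for unmasking practitioners does not fit them

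*Protocol article*

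**What the plan says.** Section 2.5.1 of the protocol article opens with a set exercise: "Pelvic floor rehabilitation consisted of 10 maximal voluntary contractions maintained for at least 6 seconds", followed by a short run of rapid contractions. Delivery is the same for everyone: "Two professional physiotherapists will provide face-to-face coaching training to the participants twice a week for 12 weeks". Home practice is also common to both arms: "all participants will be asked to follow the written instructions at home every day and record the frequency". The section then adds a weekly monitoring meeting at which "professional physiotherapists will conduct new assessments and guidance according to the intensity, frequency, and timing of the participants’ training".

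Section 2.5.2 makes this rehabilitation the background of both arms: "The observation group was combined with acupoint injection on the basis of pelvic floor rehabilitation training, whereas the control group was simply given rehabilitation training". It also says that one experienced doctor performs all the injections.

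On masking, section 2.4 states: "Given the practical nature of acupoint injection, participants and practitioners might be aware of random assignment". It then names those who are masked: "the evaluators of the research results, the statisticians of data statistics and analysis did not know about the distribution". The physiotherapists are not mentioned in that section. The Discussion concedes that strict double-blinding is not achievable and may affect the results, but says nothing about the delivery of rehabilitation.

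**The concern.** The trial's causal claim rests on the two arms differing only in the injection. The rehabilitation is not inert: by the article's own account in the Introduction and Discussion, it acts on pelvic floor muscle function, and the sample size is based on the strength of class I fibres. If the people who review and guide a woman's training each week know her arm, they may push harder in one arm. That could be enthusiasm for the new treatment, or compensation for women who do not receive it. The comparison would then estimate injection plus a difference in rehabilitation.

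Masking the outcome evaluators does not deal with this. It protects the measurement, but a woman who has trained more is in fact stronger, and a masked evaluator will record that correctly. A larger sample does not deal with it either.

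The reason offered for unmasking is the practical nature of the injection. It explains why the injecting doctor and the women know the arm. It gives no ground for the physiotherapists to know it, since nothing in the text gives them a part in the injections. A mask that is available for the staff with most contact is therefore not claimed.

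**Working it through.** **Step 1. Who could influence what, and who is masked**

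| Role | Contact with the women | Masking in 2.4 |
|---|---|---|
| Injecting doctor (2.5.2) | Observation group only | Cannot be masked; the stated reason applies |
| Physiotherapists (2.5.1) | Both arms, coaching and weekly guidance | Not named; the stated reason does not apply |
| Outcome evaluators, statisticians (2.4) | Outcome measurement and analysis | Stated to be unaware |
| Women | Own effort at home | May know the arm |

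Contact under the stated schedule: 2 coached sessions a week × 12 weeks = 24 sessions, plus one monitoring meeting a week, taken here as 12 over the treatment period. New guidance is tied to the weekly meeting only, so the 24 sessions should not be counted as further points at which the regimen is revised.

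**Step 2. The plan's own figure, for scale**

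Inputs from section 2.3: 19.37 (SD 2.26) and 21.01 (SD 2.57), one-sided α 0.025, β 0.20, 10% withdrawal. Only the absolute difference is used here; its direction is a separate matter.

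- Difference = 21.01 − 19.37 = 1.64.
- Pooled SD = √((2.26² + 2.57²)/2) = 2.42.
- Standardised difference = 1.64/2.42 = 0.678.
- The normal approximation gives 35 per group. The noncentral t gives power 0.798 at 35 and 0.809 at 36, hence 36.
- 36/0.90 = 40.

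The stated 36 and 40 reproduce and are not in dispute.

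**Step 3. Illustration under an assumed shift**

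The document gives no size for a between-arm difference in guided training. Assume a shift of s SD in strength from this cause alone, with 36 evaluable women per arm, so that √(36/2) = √18 = 4.243.

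If the injection has no effect and the shift favours the injection arm, P(false claim) = 1 − Φ(1.96 − s√18). If the injection has the planned effect and the shift favours the control arm, power = Φ((0.678 − s)√18 − 1.96).

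| s (SD) | Points (s × 2.42) | Share of 1.64 | False claim, shift to injection arm | Power, shift to control arm |
|---|---|---|---|---|
| 0 | 0 | 0% | 2.5% | 82% |
| 0.1 | 0.24 | 15% | 6.2% | 69% |
| 0.2 | 0.48 | 30% | 13.3% | 53% |
| 0.3 | 0.73 | 44% | 24.6% | 36% |

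These are normal approximations. Section 2.8 plans a Mann–Whitney test at P < .05, so the exact values would differ somewhat, but the pattern would not.

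**The case against.** Four points weigh on the other side.

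- **No strict contradiction in 2.5.1.** A reader might infer that a fixed set and weekly re-guidance are incompatible, or that staff are licensed to change the training dose each week. The text does not establish that. Read after the sentence on daily home practice, the guidance may concern only technique or adherence. This objection stands: the two paragraphs need clarifying, but no error is shown.
- **The physiotherapists are not said to be unmasked.** A reader might infer that they know the allocation. Section 2.4 says only that "participants and practitioners might be aware of random assignment" and does not tie the word for practitioners to any role. This also stands. What can be said is that nothing exempts the physiotherapists and that they are absent from the list of masked roles.
- **A journal article condenses.** Coaching manuals and staff instructions usually sit in the full protocol, and their absence here is no fault. But the article does set out who is masked and why others are not, and that reasoning does not reach the physiotherapists. Masking them would change the conduct of the trial as described; it is more than a missing detail.
- **Safeguards exist, and the remedy is partial.** The written instructions, the schedule and the pair of physiotherapists are common to both arms, and home frequency is recorded. Women who know their arm can still vary their effort at home or tell the physiotherapist. All of this is true. It makes drift a risk and not a certainty, and it limits what masking can achieve, but it does not make masking pointless.

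**Conclusion.** The point holds as a cheap improvement. As described, the staff who steer a strength-affecting treatment common to both arms are not stated to be masked, and the justification given for unmasking does not cover them. The resulting performance bias could go in either direction and would survive blinded outcome evaluation.

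Its size is unknown. The figures of about 6%, 13% and 25% for a false claim, and 69%, 53% and 36% for power, rest wholly on assumed shifts of 0.1, 0.2 and 0.3 SD. They show sensitivity and are not estimates. A reader might take them as this trial's actual error rates, or conclude that its result will be biased; the document supports neither, and nothing in it indicates that coaching will in fact depend on the arm.

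**What to change.** - **Section 2.4:** state that the physiotherapists who coach and hold the monitoring meetings are not told the allocation, and that women are asked not to disclose it to them.
- **Section 2.5.1:** say whether the weekly guidance may alter the set regimen, and that the same rule applies in both arms. Which regimen or rule is used is for the sponsor.
- **Reporting:** compare by arm the home-training frequency already recorded and the coached sessions attended, so that any difference in background rehabilitation can be seen.

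The cost is a few sentences, an instruction to staff and participants, and one descriptive table. Home frequency is already collected; attendance needs only a session log if none is kept. No extra patients, staff or procedures are required. The downside is that the masking will be partial: some women will disclose their arm, and effort at home may still differ. The table would make a difference visible but would not prevent it.
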